#### The principle of blinded

2.4.2

The evaluator will evaluate the results after the end of the trial, in which the evaluator cannot be the acupuncturist performing the operation, and until the end of the trial, the evaluator does not know the group distribution. Data statisticians are also ignorant of the distribution of groups before making statistical data. The trial will fully follow the blind method, but patients and acupuncturists cannot follow the blind method because there is no sham acupuncture group in the control group.

#### In vitro fertilization procedure

2.4.3

All selected patients will be treated with the GnRH-a/r-FSH /HMG/HCG long agonist protocol.

On the 21st day of menstruation, a 1-time intramuscular injection of long-acting Tripraline (French Signes) 1.1 to 1.50 mg will be given to achieve downregulation. FSH, LH, and estradiol levels will be measured by fasting blood sampling after 14 days of downregulation. After reaching the downregulation standard (B ultrasound monitoring follicle diameter < 5 mm; endometrial thickness <5 mm; LH < 5 mIU/mL, estradiol < 50 pg/mL), the treatment with gonadotropin (Gn) (Gonafen, 75 IU/ dose, made by Merck serono) for 125 to 300IU superovulation will begin. Gn dosage was determined according to the number of basal sinus follicles, the level of basal sex hormone, and the hormone level of 14 days. Gn was discontinued and HCG (produced by Zhuhai Lizhu Biological Pharmaceutical Co, LTD, [name]) was intrusculated 5000 to 10,000 units when there was at least 1 follicle with a > diameter of 18 mm, or 2 or 3 follicle with a > diameter of 17 mm. After the injection of HCG for 34 to 36 hours, the eggs were obtained by vaginal puncture under the guidance of b-ultrasound.

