**Method/Design::**

To investigate the effect of Stage by Stage Acupuncture and Moxibustion Therapy on endometrial receptivity and Pregnancy Outcome based on the theory of “Chong channel being sea of blood,” we will conduct a multicenter randomized controlled trial. Inclusion criteria are as follows: infertile women under 45 years of age who received IVF-ET or Intracytoplasmic sperm injection cycles. The study will only be applied to women who have failed repeated implantation, that is, women who have failed 3 or more embryo transplants in the past (existing frozen embryos do not require the retrieval of eggs). Those who are not prepared to receive IVF-ET or are at risk of pregnancy, have a serious medical condition, or are egg donors will be excluded. Subjects will be randomly assigned to either the acupuncture group (IVF-ET plus stage-by-stage acupuncture and moxibustion therapy based on the “Chong channel being sea of blood” theory) or the control group (IVF-ET only). The trial required a total sample size of 246 women to compare endometrial receptivity between the 2 groups. The acupuncture group will receive acupuncture and moxibustion treatment 3 times a week starting from the third day of menstruation in the ovary stimulation cycle. One menstrual cycle was one course of treatment, and a total of 3 menstrual cycles were treated. The main outcome indicator was clinical pregnancy rate. Secondary outcome indicators were the three-dimensional volume blood flow parameters (vascularization index, flow index, and vascularization flow index) of the endometrium, endometrial thickness, endometrial volume, uterine artery PI, RI, and S/D during the “implantation window period” (20–24 days after menstruation in the ovary stimulation cycle).

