### Eligibility criteria

2.1

Women admitted to the reproductive medicine center of the research hospital will be screened to determine their suitability for in vitro fertilization. All IVF indications for women, such as tubal infertility, severe male factor infertility, endometriosis, unexplained infertility, immune infertility, and anovulation infertility, were recommended for this study. The included patients must be infertile women under the age of 45 who have undergone in vitro fertilization-embryo transfer or Intracytoplasmic sperm injection cycles, who have experienced 3 or more IVF-ET failures, and who have frozen embryos and no longer need to take eggs. Exclusion criteria were severe physical diseases or contraindications to acupuncture and moxibustion, poor pregnancy and birth history, thrombotic diseases, etc.

Patients have the right to refuse to participate in the study, and they can withdraw at any time. Their consent or withdrawal would not affect their intended IVF treatment.

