#### Acupuncture intervention

2.4.4

Acupuncture and moxibustion group: Gn RH-a/r-FSH /HMG/HCG agonist long scheme plus Stage by Stage Acupuncture and Moxibustion Therapy Based on the “Chong Channel Being Sea of Blood” Theory. Treatment principle: Adjust qi and blood of Chong channel, because the abundance of Ren channel and Chong channel is a necessary condition for “pregnancy,” which is closely related to the uterus.^[11]^ We mainly use the Chong channel acupoints. Acupuncture prescription: Main acupoints: SP-4(Gongsun) (see Fig. 2), PC-6(Neiguan) (see Fig. 3). Acupoints matching: Add relevant acupoints according to menstrual cycle (follicular phase, ovulation phase, luteal phase) and type differentiation.

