In this study, we choose recurrent implantation failure (RIF), which means that female patients who have had 3 or more failed embryo transplants in the past and who have existing frozen embryos and do not need to have their eggs removed again are the subjects of this study, to rule out the influence of abortion and other factors on endometrial receptivity. The intima threedimensional volumetric blood Flow parameters, including VI (Vascularization index), FI (Flow index) and VFI(vascularized blood Flow index), are taken as the main indexes to reflect the intima tolerance, because we think lining three-dimensional volume under the blood Flow parameters can reflect the endometrium and endometrial regional Vascularization and blood perfusion of the overall situation, can more fully and objectively reflect the endometrium and endometrial blood Flow. At present, there are many factors to evaluate endometrial receptivity, including endometrial thickness, volume, morphology, local endocrine changes, and blood perfusion status. Studies have shown that endometrial volume and endometrial blood flow can more directly reflect the microenvironment of embryo implantation site than uterine artery.^[15]^ Silva and Ginther ^[16]^ found that patients with monitoring of endometrial blood flow had a better implantation rate. Santoshkumar et al's^[17]^ latest study showed that endometrial blood flow could well predict the implantation rate of IVF cycles and was not affected by the morphological manifestations of endometrium. At the same time, we believe that the “sham acupuncture group” is difficult to be truly implemented in clinical practice. Because this study aims to explore the effectiveness of stage-by-stage acupuncture and moxibustion therapy based on the “Chong Channel being sea of blood” theory in improving endometrial receptivity and Pregnancy Outcome after repeated transplantation failure, only the control group and the stage-by-stage acupuncture and moxibustion group based on the “Chong channel being sea of blood” theory were set up.

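### Entry requires frozen embryos and no further egg retrieval, yet the procedure section puts every selected patient through stimulation and retrieval

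*Protocol article*

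**What the plan says.** On who is enrolled, section 2.1 admits women with at least three failed transfers "who have frozen embryos and no longer need to take eggs". The Discussion explains the choice of population and says that women "who have existing frozen embryos and do not need to have their eggs removed again are the subjects of this study". The Abstract adds, in brackets after the definition of repeated failure, that "existing frozen embryos do not require the retrieval of eggs".

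On what is done to them, section 2.4.3 opens with "All selected patients will be treated with the GnRH-a/r-FSH /HMG/HCG long agonist protocol". It then sets out downregulation, gonadotropin stimulation and an HCG injection, and ends: "After the injection of HCG for 34 to 36 hours, the eggs were obtained by vaginal puncture under the guidance of b-ultrasound". Section 2.4.4 defines the acupuncture arm as "Gn RH-a/r-FSH /HMG/HCG agonist long scheme plus Stage by Stage Acupuncture and Moxibustion Therapy".

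On timing, the Abstract starts acupuncture on day 3 of menstruation in the stimulation cycle. The Abstract and section 2.6 both place the secondary endometrial measurements in an implantation window at days 20–24, again counted in the stimulation cycle. Section 2.6 also lists measurements before enrolment, after treatment and one day before transfer, and diagnoses clinical pregnancy (the primary outcome) by ultrasound five weeks after transfer.

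**The concern.** The population and the treatment pathway exclude each other. Women are selected because they need no retrieval, and the procedure then assigns all of them to one.

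Read literally, the plan exposes women to stimulation and puncture that its own entry criteria say they do not need. If a centre instead follows the entry criteria, it must depart from sections 2.4.3 and 2.4.4, and nothing in the article says what replaces them.

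The statistical stake is what the estimates describe. A pregnancy rate after fresh transfer and one after frozen transfer refer to different clinical situations, and blood-flow and thickness measurements taken in a stimulated cycle are made under different hormonal conditions from those taken outside one. The article does not fix which of these its primary and secondary outcomes refer to.

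**Working it through.** No arithmetic applies. The check sets the passages side by side and tests whether any reading makes them agree.

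**Step 1: the two statements**

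| Topic | Eligibility text (2.1, Discussion) | Procedure text (2.4.3, 2.4.4) |
|---|---|---|
| Embryos | Already frozen | Eggs newly collected |
| Stimulation | None implied | Gonadotropin "for 125 to 300IU superovulation will begin" |
| Retrieval | Not needed | Performed 34 to 36 hours after HCG |
| Applies to | All subjects of the study | All selected patients; restated for the acupuncture arm |

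**Step 2: readings that might reconcile them**

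- *Section 2.4.3 describes the past cycle that produced the frozen embryos.* It opens in the future tense and covers all selected patients, and section 2.4.4 adds acupuncture to the same scheme as a trial arm. The past tense at its end does not help, because the article mixes tenses elsewhere (sections 2.4.1 and 2.6).
- *Only the downregulation is meant, as preparation for a frozen transfer.* The section goes on explicitly to superovulation and retrieval.
- *The article is condensed and the frozen pathway sits in the full protocol.* Condensation could explain an absent pathway. Here a pathway is stated in detail, and it is the one that conflicts with entry. The article does not describe thawing or endometrial preparation anywhere.

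None of the three works.

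**Step 3: which schedule points depend on the stimulation cycle**

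| Point | Counted from | Affected? |
|---|---|---|
| Acupuncture start, day 3 | Stimulation cycle (Abstract only; 2 and 2.5 give three sessions a week over three menstrual cycles without naming that cycle) | Yes |
| Days 20–24 endometrial window | Stimulation cycle (Abstract, 2.6) | Yes |
| Scan before enrolment | Enrolment | No |
| Scan after treatment | End of treatment | Only through the start date |
| Scan one day before transfer | Transfer | Not directly; type of transfer undefined |
| Pregnancy scan at five weeks | Transfer | Not directly; type of transfer undefined |

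So two points are contradicted outright. In addition, acupuncture begins in the stimulation cycle but runs for three menstrual cycles, so the text does not fix where the days 20–24 scan and the transfer fall within those three cycles.

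**Step 4: how many women are concerned**

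The entry rule and section 2.4.3 both apply to everyone enrolled: 123 + 123 = 246.

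**The case against.** The contradiction between entry and procedure is hard to dispute. The fair objections concern how far it reaches.

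- *Support in the Abstract is weaker than in the body.* The bracketed remark can be read as a comment on frozen embryos rather than as an entry rule. This stands, but section 2.1 and the Discussion carry the restriction without it.
- *The schedule evidence is limited.* The acupuncture anchor rests on one sentence in the Abstract, and the SPIRIT figure (Figure 1), which may fix visit times, is not shown. This stands as a caution on timing. A figure of visits could not remove the conflict between 2.1 and 2.4.3.
- *A reader might infer that the timing of every endometrial outcome is invalid.* Section 2.6 does not support that: it also gives measurement times tied to enrolment, the end of treatment and transfer.
- *A reader might infer that the three hospitals are in fact mixing fresh and frozen transfers.* Nothing in the article says so. Section 2 requires each centre to follow the entry criteria strictly, and section 2.7 provides training and monitoring. Mixing is a risk created by the conflict, not a documented event. Training and monitoring also cannot settle which of two conflicting instructions to follow.
- *A reader might infer that such mixing would bias the comparison between arms.* Where the type of transfer is settled before randomisation, it is balanced between arms in expectation. The harm would then be to the definition of the population, to interpretation and to precision.

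**Conclusion.** The plan is wrong as written. Sections 2.1 and 3 define a population that needs no egg retrieval, and sections 2.4.3 and 2.4.4 prescribe stimulation and retrieval for that same population. The conflict applies to all 246 women and directly contradicts two timing points: the acupuncture start and the days 20–24 window for the secondary endometrial outcomes. The remaining scans are not directly contradicted, but the article leaves open whether the transfer before the primary outcome is fresh or frozen.

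The conclusion on entry against procedure rests on explicit text and needs no assumption. The conclusion on timing assumes that the missing figure does not give different anchors. The consequence for the results depends on how centres resolve the conflict, which the article does not show. The documents do not say which pathway is intended, and this point takes no view on it.

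**What to change.** 1. Reconcile the Abstract, section 2.1 and the Discussion with sections 2.4.3 and 2.4.4, so that one consistent pathway applies to enrolled women in both arms. The investigators decide which.
2. Reconcile the two timing statements, the acupuncture start in the Abstract and the days 20–24 window in the Abstract and section 2.6, with that decision.
3. Record transfer type (fresh or frozen) for every woman.
4. Establish which pathway women already recruited have followed; section 4 reports that recruitment began on July 20, 2018.
5. If both pathways were used, report results by transfer type. Adjust the primary analysis for transfer type only where the type was fixed before randomisation. Section 2.4.2 states that patients and acupuncturists are not blinded, so a type settled after allocation could be influenced by the arm, and adjusting for it could introduce bias.

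Cost: a protocol amendment, a notice to the three hospitals, one case report form field if transfer type is not already captured, and the check of women already recruited. That check is the larger share of the work if practice has differed. No change in sample size follows from this point.

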#### Acupuncture intervention

2.4.4

Acupuncture and moxibustion group: Gn RH-a/r-FSH /HMG/HCG agonist long scheme plus Stage by Stage Acupuncture and Moxibustion Therapy Based on the “Chong Channel Being Sea of Blood” Theory. Treatment principle: Adjust qi and blood of Chong channel, because the abundance of Ren channel and Chong channel is a necessary condition for “pregnancy,” which is closely related to the uterus.^[11]^ We mainly use the Chong channel acupoints. Acupuncture prescription: Main acupoints: SP-4(Gongsun) (see Fig. 2), PC-6(Neiguan) (see Fig. 3). Acupoints matching: Add relevant acupoints according to menstrual cycle (follicular phase, ovulation phase, luteal phase) and type differentiation.

**Figure 2 F2:**
[figure not shown]
SP-4 (Gongsun) location.

**Figure 3 F3:**
[figure not shown]
PC-6 (Neiguan) location.

### Intervention plan

2.5

Course of treatment: Acupuncture treatment 3 times a week, 1 menstrual cycle for a course of treatment, a total of 3 menstrual cycles.

Acupoint location: Acupoint location was established according to the national standard of the People's Republic of China—Name and Location of Acupoints GB/ t12346–2006》.

Needle selection: HUANQIU disposable sterile acupuncture needle, made by Suzhou Acupuncture and Moxibustion Products Co, LTD, has a specification of 0.30×40 mm, which diameter is 0.30 mm and length is 1.5 inches.

Operation method: After the doctor cleans the hands, the patient should be placed in the supine position to expose the skin at the selected acupoint, and local routine disinfection should be conducted after the acupoint selection. The method of lifting, inserting, or twisting is performed after fast insertion, Make patient acupoint feel acid hemp heavy distension, acupuncture doctor hand feels nervous feeling, namely “De Qi.” The abdominal acupoints adopted the method of airflow in and out slowly, and the other acupoints adopted the method of flat supplement and flat purging with the needle kept for 20 minutes.

Operators: At every study hospital, 2 uniformly trained acupuncturists with at least 2 years of clinical experience will participate in the process. The acupuncturist will be provided with treatment protocols, research intent or purpose, treatment records, and training for future monitoring.

### The measurement of results

2.6

The main outcome indicator was clinical pregnancy rate. Clinical pregnancy rate test method: vaginal b-ultrasonography was performed 5 weeks after transplantation, and clinical pregnancy was diagnosed in patients who saw fetal sac, fetal bud, and fetal heart beat.

Secondary outcome measures were the endometrial 3D volume and blood flow parameters (vascularization index [VI], flow index [FI], and vascularization blood flow index [VFI]), endometrial thickness, endometrial volume, uterine artery PI, RI, and S/D during the “implantation window period” (20–24 days after menstrual cycle of ovary stimulation). The measurement time was before enrollment, after treatment, and 1 day before transplantation. All the patients were scanned by transvaginal 3-dimensional imaging, and the same setting was used. The operation was performed by the same person.

Data were collected from the IVF center database before enrollment, 1 day after treatment and 5 to 40 weeks after transplantation, as well as from patient follow-up. We will collect data on the safety of acupuncture treatment and any adverse events from the treatment of the implementer.

### The quality control

2.7

To ensure the quality of research, all researchers must attend all training courses and pass the training examinations. They must master all the details of the experiment before they can carry it out. For example, they must master the use of randomization and fill out a Case report form. Acupuncturists should undergo strict and systematic training. The assessor should know how to collect and input data accurately and completely.

To protect confidentiality before, during and after the trial, we will collect, share, and maintain the personal information of potential and registered participants by professionals, and the assessor will pay attention to confidentiality when entering data. During the trial, all details will be recorded, including all adverse events such as needle breakage, bleeding, hematoma, fainting, severe pain, and local infection. Serious adverse events are immediately reported to the principal investigator and immediate rescue and compensation procedures are initiated.

To ensure trial quality, clinical monitors designated by the principal investigator will periodically verify all process details. All operational frequencies and procedures for this study will be reviewed by a professional independent of the investigator and sponsor. If there are significant protocol modifications (e.g., changes to eligibility criteria, outcomes, analyses), the study plan will be communicated to relevant parties (e.g., investigators, REC/IRBs, trial participants, trial registries, journals, regulators).

### Statistical analysis

2.8

SPSS v. 21.0 Windows was used for statistical analysis. All data are presented as mean ± standard deviation or percentage. Independent samples were compared using the *t* test. Descriptive statistics and bivariate tests (e.g., correlation test, *t* test, and *χ*^2^ test) will be used to summarize the sample demographics and to examine the distribution characteristics and relationships of the study results. Specifically, we will assess the overall difference (group effect) in endometrial three-dimensional volume blood flow parameters (VI, FI, and VFI) between the acupuncture group and the control group, changes during the study period (time effect), and differences in such changes (intergroup interaction) between the groups. Significant group effects or intergroup interactions will indicate significant effects of the intervention.

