### Sample size

2.2

Based on the calculation of sample size, 2 groups are proposed in this scheme. Test level α=0.05, test efficiency 1−β= 0.90. The retention rate of acupuncture and moxibustion group was based on the effective rate of acupuncture in stages on endometrial receptivity in our previous research results (27%),^[8]^ and the effective rate of subendometrial blood flow parameters in the study of acupuncture in enhancing endometrial receptivity (26.3%) in Hu et al,^[9]^ which was estimated to be 27%. In the meta-analysis based on Smith et al, the effective rate of the blank group was 10%.^[10]^ Therefore, 10% of the control group was selected as the minimum clinical test difference that might change clinical practice. In the staged acupuncture group, 27% was the smallest difference in clinical detection that could change clinical practice, and the shedding rate was 10%. According to the formula $n=\frac{1}{\left(1-f\right)}*\left[\frac{2*{\left(z_{\alpha }+z_{\beta }\right)}^{2}*p*(1-p)}{\left(p_{0}-p_{1}\right)}\right],\;\;\;\;\;p=\frac{\left(p_{0}-p_{1}\right)}{2}$,^[11]^ where n= the sample size of each group. F = shedding rate, value 0.1. P0 = effective rate of the control group, with a value of 0.1. P1 = effective rate in the stage acupuncture group, with a value of 0.27. Z_α_ = 1.65 when α=0.05 (unilateral). When 1−β = 0.90, Z _β_ = 1.28. After calculation, n = 122.12≈123. Finally, the sample size of each group was taken as 123 cases.

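### The either-or rule for VI, FI and VFI roughly doubles the false-positive rate, and its group effect appears to average in the pre-enrolment scan; one baseline-adjusted contrast would do better at 5%

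*Protocol article*

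**What the plan says.** Section 2.6 of the protocol article (The measurement of results) makes these outcomes secondary: "Secondary outcome measures were the endometrial 3D volume and blood flow parameters". It gives the schedule as follows: "The measurement time was before enrollment, after treatment, and 1 day before transplantation". So there are three scans, the first of them before any treatment.

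Section 2.8 (Statistical analysis) sets out the comparison: "we will assess the overall difference (group effect) in endometrial three-dimensional volume blood flow parameters (VI, FI, and VFI", and then "changes during the study period (time effect), and differences in such changes (intergroup interaction) between the groups". It closes with a decision rule: "Significant group effects or intergroup interactions will indicate significant effects of the intervention". No adjustment for the pre-enrolment value is mentioned, and no scan is excluded from the group effect.

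**The concern.** The plan reads as a repeated-measures analysis in which either of two tests is enough to declare efficacy. Two features look wrong.

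- **The group effect.** If it averages all three scans, it includes one that acupuncture cannot have influenced. The estimate is then diluted, and a difference already present before treatment adds directly to a contrast that the plan calls an effect of the intervention. A significant group effect suffices even if the arms show no differential change.
- **The either-or rule.** It gives each parameter two chances of a false positive, each at the full level.

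At stake is the trial's conclusion on mechanism. The Discussion calls the three flow parameters the main indexes of endometrial receptivity, and they are the only outcomes for which section 2.8 spells out an inferential rule.

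**Working it through.** **Inputs from the article.** Three scans, one before enrolment (2.6). Rule: group effect or interaction (2.8). Level and power from section 2.2: "Test level α=0.05, test efficiency 1−β= 0.90". There are 123 women per group with 10% loss, so 123 × 0.9 = 110.7, about 111 analysed per arm.

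The article gives no figure for VI, FI or VFI that could be reproduced. The 123 comes from response rates and is used here only as a headcount. Section 2.2 states a one-sided z, "1.65 when α=0.05 (unilateral", but 2.8 gives no sidedness for these tests, so I use two-sided 5%.

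**Assumptions.** Equal SD at each scan, equal correlation r between scans (0.3, 0.5, 0.7), and true effects of 0, d, d at the three scans. The article gives none of these.

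**Step 1: dilution.** Group effect = (0 + d + d)/3 = 2d/3. If the two later effects differ, it is (d1 + d2)/3 against a post-baseline mean of (d1 + d2)/2, which is again two thirds.

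**Step 2: precision.** Per-patient variance divided by squared effect:
- Group effect: [(1+2r)/3] / (4/9) = 3(1+2r)/4.
- Mean of the two later scans adjusted for baseline: (1−r)(1+2r)/2.

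The ratio is 3/[2(1−r)] = 2.1, 3.0 and 5.0 at r = 0.3, 0.5 and 0.7. The group effect taken alone needs that many times the patients. With correlation decaying over visits (AR(1)) the ratio is 1.8 to 3.4.

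**Step 3: baseline imbalance with no true effect.** Work in standard errors of a single-scan difference and let the baseline difference be 2. Given that, the group contrast has mean 2(1+2r)/3 and variance 2(1−r)(1+2r)/9. It is significant in favour of acupuncture above 1.96·√[(1+2r)/3].

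| r | mean | SD | threshold | P(significant for acupuncture) |
|---|---|---|---|---|
| 0.3 | 1.067 | 0.499 | 1.431 | 23% |
| 0.5 | 1.333 | 0.471 | 1.600 | 29% |
| 0.7 | 1.600 | 0.400 | 1.753 | 35% |

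The nominal one-tail figure is 2.5%. At a 1.5 SE imbalance the results are 10%, 10% and 8%. Averaged over all randomisations, the group test keeps its level (4.6 to 5.0% in 10,000 simulated trials).

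**Step 4: false positives under the either-or rule.** With equal correlations the group mean and the within-patient contrasts are independent, so the error rate is 1 − 0.95² = 9.75% per parameter. Simulation gives 9.2 to 9.7%; ANCOVA stays at 4.6 to 5.2%.

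**Step 5: power.** Take 111 per arm and the d that a single-visit ANCOVA detects with 90% power. This is 0.42, 0.38 and 0.31 SD at the three correlations.

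| Test | r=0.3 | r=0.5 | r=0.7 |
|---|---|---|---|
| Group effect alone | 81% | 63% | 41% |
| Interaction alone (2 df) | 78% | 84% | 88% |
| Either-or rule, each test at 5% | 96% | 94% | 93% |
| Either-or rule, each test at 2.5% | 91% | 88% | 87% |
| Two-scan ANCOVA at 5% | 98.5% | 97.8% | 97.1% |

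The either-or figure is 1 − (1 − group)(1 − interaction); at r = 0.5 this is 1 − 0.370 × 0.164 = 0.939.

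**The case against.** The strongest reply is that the plan does not lose power. A reader might infer from the group-effect row that the trial has as little as a 41% chance of detecting the effect. The documents do not support that, because either test suffices and the rule as written reaches 93 to 96%. This objection stands. The cost of the rule is its error rate; at an honest overall 5% it falls to 87 to 91%, still below the two-scan ANCOVA.

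A reader might also infer that baseline imbalance inflates the group test's false-positive rate in general. It does not. Allocation is randomised and the test's unconditional level is 5%. The 23 to 35% applies only given a 2 SE imbalance, which is uncommon.

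Third, section 2.8 never says that the pre-enrolment scan enters as a response, and a separate analysis plan could settle the model. The first part stands as a caveat. Still, the reading is the natural one: change during the study has to start from that scan, and none is excluded. The either-or rule needs no inference, because it is printed as the criterion for efficacy.

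Fourth, the interaction already uses change from baseline. That is true, but the plan lets the group effect override a null interaction.

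Finally, the general sentence on t tests in 2.8 is not tied to these outcomes, so no criticism is built on it.

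**Conclusion.** The point holds in a limited form. The either-or rule is stated and carries a false-positive rate of about 9 to 10% per parameter in place of 5%. On the inferred but natural reading that all three scans are responses, the group effect is also diluted by one third and can credit acupuncture with a difference that predates treatment.

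A single baseline-adjusted contrast on the two later scans has more power than the rule (97 to 98.5% against 93 to 96%) at about half its error rate. The dilution follows from the visit schedule alone. The power and conditional figures rest on assumed correlations and effect sizes, with equal correlation between scans; the direction was the same at every correlation examined.

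The finding does not reach the primary outcome. VI, FI and VFI are secondary, and the clinical pregnancy comparison does not use this rule. The change should be made, but the trial's main result does not depend on it.

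**What to change.** Reword section 2.8. For each of VI, FI and VFI, name one treatment contrast tested at 5%, taken from an ANCOVA or mixed model of the two post-baseline scans with the pre-enrolment value as covariate (or a mixed model with the baseline means constrained equal across arms). Report the adjusted mean difference with its 95% confidence interval. Remove the group main effect and the either-or rule as criteria for efficacy. Changes over time may still be described.

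The cost is a few sentences, settled before unblinded analysis. All three scans are already scheduled, no extra patients or visits are needed, and the named software fits the model.

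### Section 2.8 lets a significant result on secondary blood-flow indices stand as an effect of the intervention, with no matching rule for clinical pregnancy, and its either/or form exceeds the 5% level

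*Protocol article*

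**What the plan says.** Section 2.6 fixes the primary endpoint: "The main outcome indicator was clinical pregnancy rate", diagnosed by ultrasound 5 weeks after transfer. The Abstract says the same. Both places list VI, FI and VFI among the secondary outcomes. Section 2.6 gives three assessment times, one of them before treatment: "The measurement time was before enrollment, after treatment, and 1 day before transplantation".

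Section 2.8 begins with a general list of methods, including correlation, t and chi-square tests, to summarise demographics and "to examine the distribution characteristics and relationships of the study results". It then describes one specific analysis: "we will assess the overall difference (group effect) in endometrial three-dimensional volume blood flow parameters (VI, FI, and VFI", plus change over time and "differences in such changes (intergroup interaction) between the groups". It closes with: "Significant group effects or intergroup interactions will indicate significant effects of the intervention".

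No sentence in section 2.8 names pregnancy. Section 2.2 sets alpha at 0.05, described as one-sided.

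**The concern.** The closing sentence of section 2.8 is the only place where the protocol says what result will count as an effect of the intervention. The effects it relies on are defined only for VI, FI and VFI, which are secondary. Nothing confines the conclusion to blood flow, and the declared primary outcome has no counterpart rule.

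The trial is presented as evidence on pregnancy outcome as well as receptivity in women with three or more failed transfers. Followed literally, the rule would let the report announce an intervention effect on the strength of an ultrasound index when clinical pregnancy does not differ. The rule is also disjunctive: a group effect or an interaction will do. It states no direction, and section 2.8 attaches no error control to it.

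**Working it through.** **The plan's own figures.** Section 2.2 gives alpha = 0.05, so a single test on the primary outcome has a type I error of 0.05. Its sample size bears on which alpha is meant. In the standard two-proportion form, with p = (0.10 + 0.27)/2 = 0.185 and 10% dropout, n = 2(z_α + z_β)² p(1 − p)/(0.17)²/0.9.
- With z_α = 1.96: 2 × 3.24² × 0.185 × 0.815/0.0289/0.9 = 121.7, close to the stated 122.12.
- With the stated one-sided 1.65: 2 × 2.93² × 0.185 × 0.815/0.0289/0.9 = 99.5.

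The text says one-sided, but the number fits two-sided. Any decision rule therefore has to state its sidedness.

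**Side by side.**

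| Item | Sections 2.6 and Abstract | Section 2.8 |
|---|---|---|
| Clinical pregnancy | main outcome | not named; no conclusion attached |
| VI, FI, VFI | secondary | the only outcomes whose significance is said to show an intervention effect |

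**Qualifying tests.** Per index there are two: the group effect (1 df) and the group-by-time interaction, (2 − 1)(3 − 1) = 2 df with two arms and three visits. The time effect does not qualify. If the indices are modelled separately, 3 × 2 = 6 tests qualify. If they are modelled jointly, 2 do. The protocol does not say which.

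**Error rate if the tests are independent, each at 0.05.**
- One index, or one multivariate model: 1 − 0.95² = 0.0975.
- Three indices separately, any one sufficient: 1 − 0.95⁶ = 0.265.

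**Allowing for correlation between the indices.** The null was simulated in two ways: 20,000 replicates of the between-arm mean differences, and 4,000 replicates of a repeated-measures analysis. The second used 111 women per arm (123 × 0.9 = 110.7) and an assumed within-index correlation over time of 0.5. The between-index correlations are also assumed. The entries are the chance of at least one significant result among the six.

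| Between-index correlation | 20,000 replicates | 4,000 replicates |
|---|---|---|
| 0 | 26% | 24.9% |
| 0.5 | 24% | 22.6% |
| 0.7 | – | 21.8% |
| 0.8 | 18–19% | – |
| 0.9 | 16% | 16.3% |
| 0.95 | – | 14.8% |

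For one index alone, the 4,000-replicate runs gave 8.8% to 10.8%. That scatters around 9.75% with a simulation standard error of √(0.0975 × 0.9025/4000) = 0.0047.

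**The group effect.** If all three visits enter the model, the group effect averages in the scan taken before treatment. A significant group effect can therefore partly reflect a chance baseline difference, which argues for the interaction as the single contrast.

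**The case against.** The strongest defence is context. The closing sentence directly follows the repeated-measures description and uses terms defined only there. It may be meant merely to say that a group or interaction effect, rather than a time effect, is attributed to acupuncture. That is plausible as intent. But the sentence carries no limit to blood flow, and no parallel sentence covers pregnancy. Even on this reading, the either/or form inflates the error of the blood-flow claim.

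A second defence is that the exact primary test and the handling of multiplicity are commonly left to an analysis plan, which is not shown. This stands as far as it goes: the absence of a named pregnancy test or of an adjustment is not the point here. The point is a stated rule that does not match the declared primary outcome.

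Several stronger readings are tempting and not supported:
- *That the Discussion sets up a rival primary outcome.* It says the indices "are taken as the main indexes to reflect the intima tolerance", meaning the preferred markers of receptivity. A secondary domain can have a main marker.
- *That pregnancy will not be analysed.* The general list in section 2.8 includes the chi-square test, which suits a binary outcome.
- *That six tests are planned.* Six is inferred from 3 indices × 2 effects; joint modelling would leave two.
- *That the indices may be tested only after a significant pregnancy result, or that a two-sided test is mandatory.* Gatekeeping is one option among several, and section 2.2 states a one-sided level.

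**Conclusion.** The point holds in this form: the closing rule of section 2.8 conflicts with the outcome hierarchy in section 2.6 and the Abstract. Read as written, it permits an unqualified efficacy claim from secondary ultrasound indices. This follows from the text alone.

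The error-rate part is conditional. About 10% applies to one index or one multivariate model. About 15% to 26% applies if the three indices are modelled separately and any one suffices, with assumed between-index correlations from 0.95 down to 0. Every scenario examined exceeds 5%, but the upper end should not be quoted as the trial's error rate, because the protocol gives neither the modelling choice nor the correlations.

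**What to change.** In section 2.8:
1. State that the conclusion on efficacy rests on the between-arm comparison of clinical pregnancy among randomised women at the 0.05 level. State the sidedness and make it consistent with section 2.2.
2. Limit the closing sentence to effects on endometrial blood flow as secondary outcomes.
3. Name one between-arm contrast per index, for example the group-by-time interaction, in place of the either/or rule.
4. Either adjust across the three indices (Holm would use 0.05/3 = 0.0167, then 0.05/2 = 0.025, then 0.05) or label the indices supportive or descriptive.

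In section 3, a clarification is enough: the indices are the main markers of receptivity, not the primary outcome.

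The cost is wording only, with no added data collection. The downside is that blood-flow results alone can no longer support an overall efficacy claim.

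Power for pregnancy should be checked separately. The Abstract ties the 246 women to a comparison of receptivity, and the 10% and 27% in section 2.2 are described largely as receptivity rates. If those rates did apply to pregnancy, 111 evaluable women per arm would give 90.9% power two-sided or 95.1% one-sided. The protocol does not establish that they do.
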